#### Step 2: Evaluation of the Long-Term Effects

Participants will be either male or female, aged 18 to 65 years, with a new or newly recurrent ENL episode and will receive 200 mg of dovramilast twice daily. Male weights will be aligned with step 1 requirements (≥40 kg), whereas females should weigh at least 35 kg.

In a subset of participants during step 2, pharmacokinetic assessments of drug levels in the blood will be performed using plasma collected at appropriate times on day 1 and day 10 (predose and 3 hours postdose) after dovramilast treatment.

As in step 1, participants will be enrolled for an initial 7 to 10 days of treatment. If patients tolerate the drug well and respond, they will continue to receive dovramilast for 12 weeks.

Every 12 weeks of treatment, dovramilast will be discontinued to determine if ENL symptoms recur or if the ENL episode has fully recovered. If symptoms recur after 28 days within the 1-year follow-up period, dovramilast will be administered again for another 12 weeks, as indicated by individual patient needs, for up to 1 year of total dovramilast treatment duration (12 wk × 4=48 wk total). Based on individual patient clinical needs, this discontinuation test will be repeated at 6 and 9 months for a total treatment period of up to 52 weeks. While clinical care may occur more frequently as indicated by individual ENL symptoms, participants will be evaluated on days 10 and 28 and monthly during treatment, and monthly for 1 year after discontinuation of the drug (final visit).

### Inclusion Criteria

Study participants must satisfy the following criteria for enrollment in the study:

Must be 18 to 65 years old, weighing >35 kg for women and >40 kg for men.In step 1, the participants must be male. In step 2, the participants can be either male or female.Understand and voluntarily sign an informed consent document prior to any study-related assessment or procedure.Have signs or symptoms of new episodes of ENL.Able to adhere to the study schedule and other protocol requirements. Patients with stable and well-managed diabetes and hypertension can be included in the study.Women of childbearing age can be enrolled in step 2 following confirmation of safety in the initial male-only cohort, provided they are not pregnant or breastfeeding, have a negative pregnancy test at screening, comply with protocol-specified pregnancy testing, and agree to pregnancy prevention counseling (including abstinence where contraception is not culturally acceptable) during treatment and for 4 weeks after the last dose of study medication.

### Exclusion Criteria

The presence of any of the following will exclude a potential participant from enrollment:

Any significant medical condition, laboratory abnormality, or psychiatric illness that would prevent the participant from participating in the study.Daily rifampicin treatment will be excluded with a minimum washout period of 2 weeks prior to dovramilast administration. However, if rifampicin is taken only once a month as part of MDT, this will not be used as an exclusion criterion.Any condition, including the presence of laboratory abnormalities, that places the participant at an unacceptable risk if they were to participate in the study.Any condition that confounds the ability to interpret data from the study (ie, HIV, chronic hepatitis B, chronic hepatitis C, or tuberculosis in patients under active treatment). Patients with resolved tuberculosis will not be excluded from the study.Use of systemic corticosteroids or thalidomide within 7 days of study medication initiation.Pregnant or nursing females.

### Primary and Secondary Outcomes

The primary outcome is the proportion of participants achieving a complete clinical response by day 10 of dovramilast treatment. Complete clinical response is defined as a clinically meaningful improvement or resolution of ENL manifestations based on standardized clinical criteria rather than a binary presence or absence. This includes a reduction in the number, tenderness, and inflammation of ENL skin nodules, assessed clinically and supported by changes in the EESS score; resolution of ENL-associated fever based on clinical assessment and temperature recordings; and improvement or resolution of nerve pain and tenderness evaluated through neurological examination and validated pain assessment tools. Safety outcomes include the frequency and severity of AEs, graded according to the National Cancer Institute Common Terminology Criteria for Adverse Events (NCI CTCAE) version 5.0 [71], as well as laboratory abnormalities and neurological assessments. In addition, plasma and skin biopsy samples will be collected at predefined time points for exploratory evaluation of biological responses to dovramilast, including inflammatory and immunological markers relevant to ENL pathogenesis (such as circulating cytokines, acute-phase reactants, and immune cell–associated markers), and histopathological features of ENL lesions. These exploratory analyses will be descriptive and are intended to provide mechanistic insights into treatment response.

Secondary outcomes include the proportion of participants who achieve and maintain remission of ENL symptoms during treatment and for up to 12 months following cessation of the study drug. Longitudinal changes in disease severity, pain, and neurological symptoms will be assessed over time using validated instruments, including the EESS, Brief Pain Inventory, and Douleur Neuropathique 4 questionnaire. In addition, the frequency of ENL recurrence and the need for repeat dovramilast treatment cycles during the follow-up period will be documented.

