### Data Analysis

This study is designed as an exploratory phase 2 pilot trial; therefore, analyses will be primarily descriptive and longitudinal rather than inferential. All analyses will be conducted according to the intention-to-treat principle, including all participants who receive at least 1 dose of dovramilast, regardless of treatment duration, protocol deviations, or withdrawal.

Primary outcome analysis will focus on estimating the proportion of participants achieving a complete clinical response by day 10 of treatment, based on predefined clinical criteria encompassing skin, systemic, and neurological manifestations of ENL. This proportion will be summarized with descriptive statistics and corresponding confidence intervals to provide an estimate of response frequency and variability. Secondary outcomes will be assessed through longitudinal evaluation of ENL severity, pain, and neurological symptoms using validated instruments (EESS, Brief Pain Inventory, and Douleur Neuropathique 4). Changes in these measures over time will be summarized descriptively using means, medians, ranges, and graphical trend displays to assess patterns of improvement, remission, and recurrence during treatment and follow-up. The frequency and timing of ENL recurrences and the need for repeat dovramilast treatment cycles will be documented to characterize treatment durability. Exploratory laboratory and tissue outcomes derived from plasma and skin biopsy samples will be analyzed descriptively to evaluate trends in inflammatory, immunological, and histopathological markers over time.

In addition to clinical and exploratory outcomes, feasibility will be assessed as a key objective of this pilot study. Feasibility indicators include the ability to recruit and retain participants according to the protocol, adherence to study medication and follow-up schedules, completeness of clinical and patient-reported outcome data, and acceptability of study procedures. These feasibility measures, together with observed variability in outcomes and safety findings, will be used to inform decisions regarding the design, operational requirements, and scalability of a future adequately powered randomized controlled trial.

Given the pilot nature of the study, missing data will not be imputed; analyses will be based on available data, and the extent and reasons for missing data will be described and considered in interpretation.

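### The primary outcome is labelled complete clinical response, but its definition also counts clinically meaningful improvement, so partial improvers enter the complete-response proportion

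*Protocol article*

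**What the plan says.** Primary and Secondary Outcomes states: "The primary outcome is the proportion of participants achieving a complete clinical response by day 10 of dovramilast treatment". It then gives the definition: "Complete clinical response is defined as a clinically meaningful improvement or resolution of ENL manifestations", to be judged "based on standardized clinical criteria rather than a binary presence or absence". Three components follow:

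- Skin: "a reduction in the number, tenderness, and inflammation of ENL skin nodules, assessed clinically and supported by changes in the EESS score".
- Fever: "resolution of ENL-associated fever based on clinical assessment and temperature recordings".
- Nerve: "improvement or resolution of nerve pain and tenderness evaluated through neurological examination and validated pain assessment tools".

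Data Analysis describes the primary analysis as "estimating the proportion of participants achieving a complete clinical response by day 10 of treatment", summarised with confidence intervals, in everyone who took at least one dose. Research Question and Hypothesis says no formal testing is planned. Sample Size and Justification reports no power calculation and says the pilot should inform the sample size of a future multicentre trial. Future Directions adds that the findings will guide the choice of its primary end point.

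**The concern.** The label and the definition describe different events. A reader takes complete response to mean that the episode has cleared. The definition joins improvement and resolution with *or*, and two of its three components can be met while disease is still present.

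This goes beyond a missing threshold. A full protocol or analysis plan could say how large an improvement must be to count, but that would still be a threshold for improvement reported under the word *complete*.

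Because the trial is descriptive, no test or power figure is at risk. What is at risk is the meaning of the main efficacy estimate and its use in planning. A later trial that takes this proportion as its complete-response rate would be planned around a different, more frequent event.

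**Working it through.** There is no figure in the article to reproduce: it gives no expected response rate, power or precision target. The check is a reading of the definition, followed by an illustration with assumed rates.

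**Reading the definition by component**

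| Component | What must happen | Can disease remain? |
|---|---|---|
| Skin nodules | Reduction in number, tenderness and inflammation | Yes |
| Fever | Resolution | No |
| Nerve pain and tenderness | Improvement or resolution | Yes |

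The article's own ENL Case Definition shows what this allows. It requires 10 or more tender lesions. Take an assumed participant who goes from 30 nodules to 12 that are less tender and less inflamed, has no fever, and has milder nerve pain. If that is judged clinically meaningful, the participant is a complete responder. Yet 12 is at least 10, so the lesion count still reaches the trial's threshold for ENL.

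**Size of the effect**

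Let r be the share whose manifestations fully resolve by day 10, and p the further share who improve enough to meet the definition without resolving. Then:

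- complete-response proportion in the ordinary sense = r
- proportion reported under the written definition = r + p
- overstatement = (r + p) − r = p

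The overstatement in percentage points does not depend on the sample size; only the width of the interval does.

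**Illustration.** n = 40 is the step 2 maximum in Sample Size and Justification. The values of r and p are assumed, since the article gives none. The 95% intervals are exact (Clopper-Pearson): lower limit = 0.025 quantile of Beta(x, n − x + 1); upper limit = 0.975 quantile of Beta(x + 1, n − x).

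| Assumed r | Assumed p | Resolved, x/40 | 95% CI | Reported as complete, x/40 | 95% CI |
|---|---|---|---|---|---|
| 30% | 20% | 12 (30%) | 16.6 to 46.5% | 20 (50%) | 33.8 to 66.2% |
| 30% | 30% | 12 (30%) | 16.6 to 46.5% | 24 (60%) | 43.3 to 75.1% |
| 30% | 40% | 12 (30%) | 16.6 to 46.5% | 28 (70%) | 53.5 to 83.4% |
| 10% | 20% | 4 (10%) | 2.8 to 23.7% | 12 (30%) | 16.6 to 46.5% |
| 10% | 40% | 4 (10%) | 2.8 to 23.7% | 20 (50%) | 33.8 to 66.2% |

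Some of these pairs of intervals overlap and some do not. Nothing follows from that, because both proportions come from the same participants. The point is that one data set yields two different answers, and the larger carries the label that belongs to the smaller.

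**Is the EESS available at day 10?** Safety and Efficacy lists end-point assessment at day 0, day 28 and 1 year after the drug is stopped. The step 2 section has participants evaluated on day 10. A day-10 visit therefore exists, but the article does not show that the EESS is scored at it.

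**The case against.** The strongest defence is that the article describes a standardised, graded assessment, that its thresholds may sit in a fuller document, and that a descriptive pilot does not rest on one proportion. Much of this stands, and it rules out several stronger readings that a reader might infer.

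- **That any improvement counts.** Not supported. The improvement must be clinically meaningful under standardised criteria, and a participant with persisting ENL fever would not qualify.
- **That a non-binary definition cannot be analysed as a proportion.** Not supported. The words "based on standardized clinical criteria rather than a binary presence or absence" most naturally describe how manifestations are judged. Dichotomising a graded assessment is ordinary practice once a cut-off is fixed, and a condensed article may leave the cut-off and the combination rule to the full document.
- **That participants without fever or nerve pain at baseline are credited automatically.** This is inference, as no rule is stated for absent components. Under the case definition every participant has skin lesions, so nobody qualifies wholly by default.
- **That the primary outcome decides who stays on drug.** Not stated. The step 1, step 2 and Interventional Methods sections refer to tolerability and response or benefit without naming the primary outcome. The open-label, single-arm design is disclosed under Strengths and Limitations and is a separate matter.

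The article also has a secondary outcome on achieving and maintaining remission, and reports the EESS and pain scales over time. Planners of the next trial would thus have other information, which limits the harm. It does not remove it: the remission outcome is not stated for day 10, and the primary estimate would still carry the wrong name.

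**Conclusion.** The concern holds as a mismatch between label and definition. Following the written rule, partial improvers whose improvement is judged clinically meaningful, and whose fever has resolved where present, are reported as complete responders. A cut-off stated elsewhere would not cure this.

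The overstatement equals the share of such participants. That share cannot be known from the article; it is 20 to 40 percentage points in the illustration only because those shares were assumed. No test, error rate or power statement is affected. The correction is inexpensive, but it concerns the primary outcome and changes what its estimate can be said to show, so it should be made before analysis.

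**What to change.** 1. Keep the existing composite and rename it *clinical response* (improvement or resolution).
2. Report separately, among all dosed participants, the proportion with *complete response*: resolution at day 10 of every ENL manifestation present at baseline, meaning skin, fever, nerve and any other EESS item scored above zero at baseline. Requiring zero only on the lesion, fever and nerve items would not suffice. The article lists 10 EESS items, and pain, bone pain, peripheral oedema, joint or digit inflammation and lymphadenopathy could then persist in a complete responder.
3. Report the change in total EESS from day 0 to day 10 with a 95% confidence interval.
4. Give fever and nerve response among those affected at baseline, so that absent components do not blur the result.
5. Confirm that the EESS is scored at day 10, and reconcile Safety and Efficacy with the step 2 visit schedule on this point.
6. Document the change before analysis. Apply the same rule to step 1 and step 2 wherever a day-10 EESS was recorded, and state how many participants lack one.

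**Cost.** A small documented amendment, not just an edit of wording: the trial is open-label, step 1 was completed in 2020, and 15 participants had been recruited by April 2026. Data collection is expected to run to September 2027, so there is time. The complete-response proportion can be no higher than under the present definition and will probably be lower.

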### Discontinuation of Treatment or Removal From the Study

A participant can be discontinued from ongoing drug treatment upon the occurrence of AEs related or unrelated to the drug treatment. If a participant fails to return for 1 or more follow-up appointments, data may still be collected upon attendance of the remaining appointments for up to 1 year after the last date of drug administration.

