### Safety and Efficacy

Primary and secondary end points for efficacy, as explained above, will be assessed on day 0, day 28, and 1 year after study drug cessation. The severity of any toxicity will be graded according to version 5.0 of the NCI CTCAE. Summaries of demographics, disposition, study drug exposure, protocol violations, and AEs will also be made.

An independent DSMB oversees trial conduct and participant safety. The DSMB reviewed safety data from the initial safety cohort (step 1) prior to progression to the expanded treatment phase (step 2). Ongoing safety oversight includes periodic review of AEs, protocol deviations, and overall study conduct. Study monitoring is conducted in accordance with Good Clinical Practice and NHRC ethical guidelines to ensure data quality, protocol adherence, and participant protection.

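### When follow-up is incomplete, remission maintained for up to 12 months, taken as a proportion on available data, does not estimate 12-month remission

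*Protocol article*

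**What the plan says.** All references are to the protocol article.

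- **Primary and Secondary Outcomes** makes durability a yes/no outcome per participant, "the proportion of participants who achieve and maintain remission of ENL symptoms during treatment and for up to 12 months following cessation of the study" treatment.
- **Data Analysis** sets the population as everyone dosed, "including all participants who receive at least 1 dose of dovramilast, regardless of treatment duration, protocol deviations, or withdrawal", and the missing-data rule, "missing data will not be imputed; analyses will be based on available data". It adds that the amount of and reasons for missing data will be described and weighed in interpretation.
- **Data Analysis** also says: "The frequency and timing of ENL recurrences and the need for repeat dovramilast treatment cycles will be documented to characterize treatment durability". It names no censoring rule and no time-to-event estimate.
- **Safety and Efficacy** says that the primary and secondary efficacy end points "will be assessed on day 0, day 28, and 1 year after study drug cessation".
- **Step 2: Evaluation of the Long-Term Effects** schedules monthly visits for a year off drug.
- **Discontinuation of Treatment or Removal From the Study** foresees gaps: "If a participant fails to return for 1 or more follow-up appointments, data may still be collected upon attendance of the remaining appointments".

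**The concern.** Whether remission lasts 12 months is decided at different times for different people. A relapse seen at month 3 fixes the answer at month 3. A participant in remission when contact ends at month 8 has no 12-month answer. Whether a participant's status is known thus depends partly on the outcome itself.

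The text allows two ways to form the proportion. One drops participants without a 12-month status, which follows from the available-data rule and the 1-year assessment point. This over-represents relapsers. The other keeps every dosed participant and reads up to 12 months as letting a short relapse-free record count as maintained, which credits relapse-free time that nobody observed. Neither estimates remission at 12 months.

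Under Future Directions, the findings are to guide the end points, sample size and treatment length of a later randomized trial. A remission rate whose error changes sign with an unstated denominator is weak input for that.

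**Working it through.** The document gives no remission rate, loss rate or power figure, so there is nothing of its own to reproduce. The check uses assumed rates.

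**Assumptions.** Relapse and loss are independent, each with a constant rate over the 12 months off drug. True 12-month remission S is 30%, 50% or 70%, and loss D over the year is 10%, 20% or 30%.

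**Formulas** (time in years):
- Relapse rate λ = −ln S; loss rate μ = −ln(1 − D).
- Relapse observed before loss: R = λ/(λ+μ) × (1 − e^−(λ+μ)).
- Followed to month 12 without relapse: F = e^−(λ+μ) = S(1 − D).
- Unresolved participants dropped: F/(F + R).
- Unresolved participants counted as maintained: 1 − R.

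**Worked case, S = 50%, D = 20%.** λ = 0.693, μ = 0.223, F = 0.400, R = 0.454. Dropped: 0.400/0.854 = 46.8%. Counted as maintained: 1 − 0.454 = 54.6%.

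| True remission | Loss | Unresolved dropped | Unresolved counted as maintained |
|---|---|---|---|
| 30% | 10% | 28.7% | 32.9% |
| 30% | 20% | 27.2% | 35.9% |
| 30% | 30% | 25.6% | 39.1% |
| 50% | 10% | 48.5% | 52.3% |
| 50% | 20% | 46.8% | 54.6% |
| 50% | 30% | 44.9% | 57.1% |
| 70% | 10% | 68.8% | 71.4% |
| 70% | 20% | 67.4% | 72.9% |
| 70% | 30% | 65.8% | 74.5% |

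With D = 0, both columns equal S.

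**Kaplan-Meier on the same data.** In 20,000 simulated trials of 40 participants, the 12-month estimate averaged within 0.1 point of a true 50% at 20%, 30% and 50% loss, and of a true 70% at 30% loss. Its standard deviation was about 8 to 10 points. Loss was generated independently of relapse, so this shows how the method behaves under that assumption. It does not show that the assumption holds in this trial.

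**Is incomplete follow-up realistic?** The Results section ends data collection in September 2027. Counting back 365 days off drug and 84 days for one 12-week course from 30 September 2027, the last first dose with complete follow-up falls on 8 July 2026. Step 2 recruitment began in September 2024, and 15 participants had been recruited by April 2026. If all 15 belong to step 2 (the text does not say), the pace is 15/19 = 0.79 per month. That gives about 15 + 3 × 0.79 = 17 participants by July 2026, and 25/0.79 = about 32 more months to reach 40. Anyone enrolled after that date would be cut off before month 12, unless collection is extended.

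**Cut-off alone, true 50%.** If a quarter of participants have only 6 months of follow-up, the two readings give 45.6% and 55.2%. If half do, they give 38.7% and 60.4%.

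**The case against.** The best defence is that the article names an outcome and not an estimator. A Kaplan-Meier figure at 12 months is itself a proportion, needs no imputation and uses all available data, so it would satisfy both sentences. Denominators and censoring often sit in an analysis plan, which is not shown. Timing of recurrence will be recorded, missing data will be described, and the outcome is secondary in a pilot without tests.

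Much of this stands. It limits the importance of the point and shows that the remedy fits the stated rules. It does not remove the point. The article does fix the yes/no form, the available-data rule and the 1-year assessment, and its only stated methods are descriptive. Describing missing data does not correct a proportion that they distort, and recording recurrence dates does not by itself bring censored time into the estimate.

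Three stronger inferences are not supported:
- **Relapsers always have a known status.** Only relapses seen before contact ends are known. A later relapse is as unknown as a non-relapse.
- **The durability figure is certain to be biased.** With complete follow-up there is no bias, and the documents give no loss rate.
- **The error is 8 to 12 points.** That is the distance between the two readings at a true 50% with 20% to 30% loss (54.6 − 46.8 = 7.8; 57.1 − 44.9 = 12.2). No single analysis incurs it.

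**Conclusion.** The point holds as a should-fix matter of analysis choice. As worded, the outcome estimates 12-month remission only if follow-up is complete. Otherwise it is too low when unresolved participants are dropped and too high when they are counted as maintained.

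At a true 50%, the error is about 3 points down or 5 points up with 20% loss, and about 5 down or 7 up with 30% loss. Across the assumed true rates it is about 1 to 3 points with 10% loss. For scale, sampling variation is about 8 points (one standard deviation) with 40 participants, so in the milder scenarios the bias is smaller than chance error. Unlike chance error, it has a fixed direction once a reading is chosen. All these sizes rest on assumed constant, independent rates. Loss related to ENL status would change them and would also bias Kaplan-Meier.

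What is affected is a descriptive durability estimate and its use in planning. No hypothesis test depends on it.

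**What to change.** In Primary and Secondary Outcomes and in Data Analysis:

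- Report remission maintained at 3, 6 and 12 months by Kaplan-Meier, with 95% confidence intervals and numbers at risk.
- Present step 1 and step 2 separately, because their first courses differ in length (28 days and 12 weeks).
- Measure time from the end of the first treatment course to first recurrence. Count participants who never remit as failures at time 0, and censor the others at the last visit with known ENL status.
- State that the estimate assumes loss is unrelated to relapse.
- Keep recurrence counts, repeat cycles and remission after the last cycle as supporting description. Step 2 re-treats new episodes, and a participant who relapses once and then stays well is a failure in the main estimate. That later remission should remain visible.

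The cost is revised wording and a few lines of code. Step 2 visits are already monthly and recurrence timing is already to be recorded. For step 1, the article states no monthly schedule, so censoring uses whichever visits recorded ENL status. The downside is slightly wider intervals at month 12, where few remain at risk.
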